
##### Motor planning

Motor planning will be assessed using a motor imagery task during which functional MRI signal is recorded. Motor imagery involves mental simulation of a movement, without actual execution of that movement. It can be used as a tool to generate cortical motor states without movement production. As is evident by the presence of scapular dyskinesia, peripheral motor control is altered in NA. With motor imagery, changes in central motor control can be assessed, while controlling for alterations in peripheral factors. Empirical evidence shows that first-person motor imagery tasks are sensitive to motor control variables and use central neural mechanisms involved in action planning [28–30]:A.Motor imagery task-based functional MRIChanges (as the result of rehabilitation and as the result of NA (assessed in the sub-study) in the neural mechanisms underlying motor planning and representations will be quantified by changes in the magnitudes of mean functional MRI signal, blood-oxygen-level-dependent (BOLD) activity associated with motor imagery during the Hand Laterality Judgment task (HLJT) (see “B”).Analyses of the functional MRI data will primarily be focused on the following brain regions: the extrastriate body area, the posterior parietal cortex in the intra-parietal sulcus region, and the precentral and postcentral gyri. These a priori regions of interest for analysis of functional MRI magnitude differences are chosen based on previous research using the same motor imagery task [1, 28, 30–32]. Additionally, we will employ a whole brain exploratory analysis of functional changes in NA outside these canonical motor imagery regions (see also “Exploratory outcomes”).Participants’ respiration will be recorded during the functional MRI scan to be able to control for noise introduced in the data.B.Performance on the motor imagery taskThe HLJT [33] assesses central representations and planning of movements involving the upper extremity. Participants are asked to judge the laterality of line drawings of hands. The hands vary in laterality (left or right), view (palmar or dorsal) and degree of rotation (rotated − 135°, − 105°, − 75°, − 45°, 45°, 75°, 105°, 135° from the upright position). Participants are instructed to use their own hands as reference (i.e. imagine moving their upper extremity to match the hand shown on screen), without actually moving their upper extremity. As participants perform this task in the MRI scanner, they cannot rely on visual information to perform the task. The task consists of 32 blocks of 8 trials. The inter-trial interval ranges from 2000 to 3000 ms. Before each block, participants are instructed to place their hands in one of four positions: both hands with palms facing up, both hands palms facing down, one hand palm up (left/right) and one hand palm down (right/left). With this manipulation, participants use of first-person motor imagery can be checked through assessment of the posture effect: when using first person motor imagery, participants are faster for stimuli with a view that is congruent with the current posture of their own hand than for stimuli with a view that is incongruent with the posture of their hand [28]. First-person motor imagery use can further be corroborated by the effect of orientation: participants are faster for medially oriented stimuli that are associated with biomechanically easy movements towards the body midsagittal plane, than for laterally orientated stimuli, that are associated with biomechanically difficult movements away from the body midsagittal plane [28]. Participants are to report whether the hand drawing on display presented a left or right hand by pressing the corresponding button with their left or right foot.Behavioural performance on this task is evaluated by means of response times (i.e. time from stimulus onset to button press) and error rates (i.e. the number of incorrect trials divided by the total number of valid trials).During the task, alertness is monitored with an eye monitor and bipolar surface electromyography (EMG) over both thumbs is performed, to monitor muscle activity indicative of hand movements and exclude the influence of overt movements.

#### Other parameters

Some measures will be collected to describe the study population and if applicable, to correct for possible confounding effects:A.Demographics: demographic data that will be collected includes age, sex and education levelB.NA characteristics: data on several characteristics of patients with NA will be collected. These include disease onset and duration, history of prior attacks and use of medication. Other characteristics may include, presence of atrophy, pattern of motor paresis, mechanical sensitivity of the plexus to pain, maximal severity of paresis during the attack and duration of primary pain.C.Comorbidity: relevant information on comorbid conditions and medication use will be collected.D.Motor imagery ability: there are individual differences in motor imagery ability [34]. As a subject’s ability to imagine movements might affect his/her performance on the motor imagery tasks in this study, motor imagery ability is assessed with the short version of the Kinesthetic and visual imagery questionnaire (KVIQ-10)*.* The KVIQ-10 assesses the clarity of the image (visual), and the intensity of the sensations (kinesthetic), that the subject is able to imagine from the first-person perspective [35].

#### Exploratory outcomes

In addition to its primary and secondary outcomes, the NA-CONTROL study includes some exploratory outcome measures that have not been used before to study NA or any similar patient populations. They were added to the study to gain additional insight in the underlying mechanisms of the residual complaints in this disorder.

##### Cerebral (re)organisation

Cerebral (re)organisation in NA will further be explored by means of additional MRI scans. For this purpose, functional and high-resolution anatomical images of the whole brain will be acquired on a 3 T Siemens whole body scanner at the Donders Centre for Cognitive Neuroimaging. An eye monitor will be utilised during the MRI scanning to monitor alertness. In addition to the secondary MRI outcome (i.e. the HLJT motor imagery task-based functional MRI signal), two different neuroimaging markers of cerebral organisation will be used:A.Functional (re)organisation in restParticipants will be asked to lie still, think of nothing in particular and look at a fixation cross while 7 min of resting-state functional MRI data are obtained.Changes in functional activity and connectivity of several brain areas and cognitive resting-state networks (including the sensorimotor, fronto-parietal and executive control networks) will be analysed primarily with independent component analysis techniques on resting-state functional MRI data [36].B.Structural (re)organizationChanges in cerebral grey and white matter will be assessed using structural brain analysis based on anatomical T1-weighted MRI scans. We will perform voxel-based morphometry, a validated and fully automated technique for computational analysis of differences in global and local grey and/or white matter volume [37].As this part of the study is exploratory, analyses of the resting-state functional MRI data and structural MRI data will not be focused on a priori regions or networks of interests. In addition to the resting-state functional MRI and structural MRI scans, a new first-person motor imagery is employed to further assess motor planning and representations.C.Neuromotor Encoding in Neuromuscular Scapular dyskinesia task (NENS-task)This first-person motor imagery task was specifically designed to investigate the impact of central motor planning in the clinical phenomenon of scapular dyskinesia. Participants are asked to imagine making pointing movements with their left or right elbow (novel movement) or finger (trained movements) towards targets shown on a computer screen, and to indicate with a right-foot button press when they have finished imaging the movement (i.e. when they have reached the target with the specified body part). Performance is evaluated by means of response times. Response time is defined as the time from stimulus onset to button press.For the NENS task, bipolar EMG of both serratus anterior muscles is used, to monitor muscle activity and exclude the influence of overt movements. The NENS task is performed outside the MRI environment, seated behind a computer screen.

### Randomisation and blinding

Patients with NA will be randomly assigned to either the experimental intervention or to the usual care in a 1:1 ratio. Patients are randomized using a Good Clinical Practice (GCP)-compliant system (Castor Electronic Data Capture), which employs stratified, variable block randomisation. To prevent uneven distribution of certain characteristics across groups, randomisation will be stratified according to two factors: sex (male/female) and age (4 blocks: 18–30, 30–42, 42–54, > 54 years). Randomisation will be performed on site (at the Donders Institute for Brain Cognition and Behaviour, Centre for Cognitive Neuroimaging) after the participant has completed the baseline measurement (see Table 1).

Due to the project design, it is not possible to blind participants or the assessor. Participants will inevitably know whether they are receiving the rehabilitation programme or usual care. The assessor cannot be blinded either, for multiple reasons: all assessments are performed by a single assessor; as the number of assessments differs across groups, the assessor will know which participant belongs to which group; as the rehabilitation programme takes place at the assessor’s workplace facility, the assessor could be un-blinded on encountering a participant visiting the facility for treatment.

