#### Data management system

Most data are collected through laboratory-based measurement systems, or entered directly into the electronic case report form (CRF) in a GCP-compliant electronic data management system (Castor EDC, www.castoredc.com). This system utilises a log system with an automated audit trail. The Delegation of Responsibilities Log will identify all individuals responsible for data collection and handling, and management of the database.

A data management plan, detailing location of and access to study data and the code list, method of coding, back-up, locking and archiving of data, code list and analysis files has been submitted to and approved by the Board of Directors of the Radboudumc.

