### Statistics and data analysis

#### Proposed analysis

All continuous variables will be summarised as the number of (missing) observations, mean, standard deviation, median and range. Categorical variables will be summarised as the number of (missing) observations and number and percentage in each category. This will be done separately for each time point (baseline, outcome measurement(s) and follow up) and for the change from baseline for each intervention group.

The primary clinical outcome (SRQ-DLV score) and most other clinical outcomes are linear or quasi-linear. Group differences in the effects of the intervention on primary and secondary outcome measures and the influence of possible effect modifiers will be investigated using generalised estimated equations analysis. If necessary, analyses will be adjusted for group differences in functional capability of the upper extremity (SRQ-DLV score), age and sex at baseline. Data will be analysed according to the intention-to-treat principle. Data will be appropriately transformed if necessary, to satisfy modelling assumptions. Prior to locking of the data, a statistical analysis plan will be drawn up and approved by a statistician and the principal investigator.

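### The printed age strata overlap at 30 and 42, and the analysis adjusts for the stratification factors sex and age only conditionally

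*Protocol article*

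**What the plan says.** Under Randomisation and blinding, the article states that "randomisation will be stratified according to two factors: sex (male/female) and age". The age factor is given as "4 blocks: 18–30, 30–42, 42–54", with a fourth band strictly above 54 years. Patients go to "either the experimental intervention or to the usual care in a 1:1 ratio", through an electronic system ("Castor Electronic Data Capture), which employs stratified, variable block randomisation"). On place and timing it says "Randomisation will be performed on site", after the baseline measurement. It does not say who operates the system, or whether the age band is typed in or derived from a recorded age or date of birth.

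Under Proposed analysis, the model is a generalised estimating equations analysis, and on covariates the article says: "If necessary, analyses will be adjusted for group differences in functional capability of the upper extremity (SRQ-DLV score), age and sex at baseline". Further detail is left to a statistical analysis plan to be approved before data lock.

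**The concern.** Two statements about the same two factors do not fit together well.

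First, the age bands are an operative part of the allocation rule, and as printed they do not partition age. A reader who wants to rebuild the strata, whether to check balance or to use age band as a covariate, cannot place patients aged 30 or 42.

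Second, the analysis treats age and sex as optional covariates, triggered by an observed difference between the groups. Stratification is there to keep the groups close on exactly these factors, so the trigger would seldom be met for them, and the usual result would be a model without the stratification factors. If age or sex predicts the outcome, such a model takes no credit for the balance that the design created, and its standard errors tend to be too large. The condition also leaves a choice of model to be made after the data are seen. The article states this rule itself, so it is more than a detail deferred to the analysis plan.

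**Working it through.** **1. Do the bands partition age?** Inputs: the four bands in Randomisation and blinding, and the minimum age of 18 in the inclusion criteria. Read each range as including both ends and the last band as strictly above 54, in completed years. Counting the bands that contain each age from 18 to 90:

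| Age | Bands that contain it |
|---|---|
| 30 | 18–30 and 30–42 |
| 42 | 30–42 and 42–54 |
| 54 | 42–54 only |
| every other age, 18 to 90 | exactly one |

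So exactly two ages are ambiguous.

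**2. How many patients could be affected?** The article gives no age distribution at enrolment, so this rests on assumption. Let q be the share of patients at each of the two ages. The expected number among 50 is 50 × 2q, and the chance of at least one is 1 − (1 − 2q)^50.

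| Assumed q | Expected number of 50 | Chance of at least one |
|---|---|---|
| 1% | 1 | 63.6% |
| 2% | 2 | 87.0% |
| 3% | 3 | 95.5% |
| 4% | 4 | 98.5% |

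An even spread of ages from 18 to between 65 and 75 (also assumed) covers 48 to 58 whole-year ages. Two of these are ambiguous, so the share is 2/58 = 3.4% to 2/48 = 4.2%, or 1.7 to 2.1 of 50 patients. That lies inside the range above.

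**3. How many strata are there?** 2 sexes × 4 age bands = 8 cells, and 50/8 = 6.25 patients per cell on average. Removing the overlap changes neither figure, and no sample size or power figure depends on it.

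**4. Do non-overlapping bands cure it?** With 18–29, 30–41, 42–54 and above 54, every age from 18 to 90 falls in exactly one band. The same is true of 18–30, 31–42, 43–54 and above 54. Both leave age 54 where the text puts it. The article does not show which of the two, if either, the system uses.

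**5. Design against analysis.** Sex and age define the strata unconditionally, but enter the model conditionally. If together they explain a fraction R² of the outcome variance and the arms are balanced on them, the unadjusted standard error is larger than the adjusted one by a factor of about 1/√(1 − R²). The article gives nothing from which R² could be taken, so this part cannot be sized. Its direction is towards lost precision, not towards bias in the estimate.

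**The case against.** **The line may carry its own convention.** The strict sign before 54 implies that the third band includes its upper limit. Applied throughout, that would put 30 in the first band and 42 in the second. But the first band must also include its lower limit, because 18-year-olds are eligible, so the text supports inclusion at both ends and never says which governs at 30 and 42. The inference is reasonable, but it is not a stated rule.

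**Shared cut-points are common shorthand on a continuous scale.** On exact age, only a patient precisely at a cut-point would be ambiguous. That stands, and the count of 1 to 4 therefore depends on reading age in completed years. The article does not say which is meant. The readings also differ at the top: a patient aged 54 and a half is above 54 on exact age, but in the third band in completed years. That is a further reason to state the unit.

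**The system may already hold a clean cut-off.** This may well be so. The article describes its electronic data system with the words "This system utilises a log system with an automated audit trail", and the stratum used for each patient may be on record. The error may then be in the printed text alone.

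**The covariate set belongs to the analysis plan.** Detail does belong there, and that plan is not shown. But the article commits to a conditional rule, and the plan should replace it rather than inherit it.

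**A stronger reading to avoid.** A reader might infer that unblinded on-site staff could put a boundary-age patient in whichever stratum gives the preferred arm. The assessor does know earlier allocations, and cells average about six patients. But steering would need hand entry of the band, a predictable next assignment in at least one of the two strata, and different next assignments in the two. The article says none of this. Its reasons for not blinding the assessor concern knowledge of a patient's group after allocation, and block sizes vary, which works against prediction.

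**Conclusion.** The point holds as a minor one. In completed years the printed bands overlap at 30 and 42 and nowhere else, so the strata cannot be rebuilt from the text for patients of those ages. About 1 to 4 of 50 patients would be involved, if each of the two ages holds 1% to 4% of patients. The effect on the treatment estimate should be slight, because a patient placed in either band is still allocated 1:1. The documents do not support a breach of allocation concealment.

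The conditional adjustment is the part more worth changing. Sex and age are design factors, and their place in the primary model should not depend on the differences observed. The gain is in precision and in removing a data-driven choice; its size cannot be given without knowing how strongly sex and age predict the Shoulder Rating Questionnaire score.

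**What to change.** 1. Look up the cut-offs set in the randomisation system and print them as non-overlapping bands, stating whether age is in completed years. If that is the system's setting, 18–29, 30–41, 42–54 and above 54 would do. Recruitment has run since March 2018, so the text should follow the system and not the reverse. A last band starting at 54 should not be printed unless the system uses it, because in completed years the present text puts 54 in the third band.
2. Confirm that the system derives the band from a recorded age or date of birth, and that the stratum used at randomisation is kept in the trial data.
3. Replace the conditional rule with a primary model that always includes sex and age, with age entered either as the stratum used at randomisation or as a continuous variable.

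The cost is one corrected line, one check of system settings and one sentence in the analysis plan. Sex takes 2 − 1 = 1 degree of freedom. Age takes 4 − 1 = 3 as bands, or 1 as a linear term. The total is 4 or 2, from 50 patients. Both variables are already collected, so no new data are needed and the sample size does not change.

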### Withdrawal procedures

Participants can choose to withdraw their consent and leave the study at any time, without specifying the reason. No additional assessments will be obtained after a subject withdraws. Data that have been collected up until that point will be used for analyses. Participants have consented to this as part of the original informed consent. Patients that want to withdraw from the study can continue with the rehabilitation programme outside the trial if they wish to do so.

The investigator or a member of the treatment team can decide to withdraw a subject from the study for urgent medical reasons. Patients with NA who have a recurrent attack during their participation will be withdrawn from the study.

If a patient is withdrawn from the study before their visit to the expert outpatient clinic, they are asked to come to the Rehabilitation or Neurology outpatient clinic for a single interdisciplinary visit, to confirm their diagnosis of NA and provide treatment advice as usual.

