#### Primary outcome

##### Functional capability of the upper extremity

The primary outcome measure for the clinical part of the RCT is the change in SRQ-DLV score from baseline to post intervention. The SRQ-DLV is a reliable and validated questionnaire measuring functional capability of the shoulder, arm and hand [16] and has been shown to be sensitive to (changes in) functional capability of the shoulder in patients with NA [14].

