#### Missing data

Throughout data collection, measures will be taken where possible to minimise the occurrence of missing data. These measures include those mentioned under “Patient retention” and clear communication with individuals involved in data collection.

Once data collection is complete, the extent of missing data will be evaluated. Any patterns in missing data will be explored, especially in relation to the intervention groups. Missing data will be imputed if necessary and if possible.

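### Patients withdrawn after randomisation for a recurrent attack or on urgent medical grounds have no outcome assessment described, so primary outcomes the intention-to-treat analysis needs are avoidably missing

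*Protocol article*

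**What the plan says.** All the text is in the protocol article.

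- **Withdrawal procedures.** The first paragraph deals with participants who withdraw consent. It says "No additional assessments will be obtained after a subject withdraws" and then "Data that have been collected up until that point will be used for analyses". The second paragraph allows the investigator or a treatment-team member to withdraw a patient on urgent medical grounds, and adds: "Patients with NA who have a recurrent attack during their participation will be withdrawn from the study". The only contact described after withdrawal is one clinic visit for diagnosis and advice, offered to patients who had not yet been to the expert clinic.
- **Functional capability of the upper extremity (primary outcome).** The primary outcome "is the change in SRQ-DLV score from baseline to post intervention".
- **Study description.** Randomisation is at the end of the baseline session. The next assessment of both arms is at 18 weeks, after which the usual-care arm starts the programme.
- **Proposed analysis.** "Data will be analysed according to the intention-to-treat principle". Group differences "will be investigated using generalised estimated equations analysis".
- **Missing data.** "Missing data will be imputed if necessary and if possible".

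**The concern.** Intention to treat needs an outcome from every randomised patient, whatever happens after randomisation. Here the protocol itself ends participation after a post-randomisation event and describes no later outcome measurement.

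The event is not neutral. The Background describes an attack as bringing acute severe arm pain and weakness with loss of function. The SRQ-DLV measures functional capability of the shoulder, arm and hand. Patients withdrawn for this reason would plausibly have scored worse than those who stayed.

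A statistical analysis plan can choose a method for missing data, but it cannot bring back scores that were never collected. At stake is whether the week-18 comparison describes all randomised patients or only those who had no recurrence and no medical withdrawal.

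**Working it through.** No figure in the protocol is being disputed. The check sets the rules side by side and then shows how any bias would scale.

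**Step 1: what a withdrawn patient contributes.** Randomisation comes first and the withdrawal rule acts afterwards. There is one assessment in the randomised period, at week 18. A patient withdrawn before it has a baseline score only, so the change score is undefined. A recurrence after week 18 leaves the randomised primary comparison intact. It affects only follow-up and the usual-care arm's later programme.

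**Step 2: what the analysis can do with that.** In its standard unweighted form, a generalised estimating equations analysis generally needs data to be missing completely at random. That is implausible when the trigger is a new attack. Imputation would have to borrow from patients of the same arm and similar baseline who had no attack, because no post-attack scores exist. It would fill in values as if the attack had not happened.

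**Step 3: whether the arms could differ.** Under Randomisation and blinding, neither participants nor the assessor are blinded. Under Patient retention, the intervention arm has five weekly, two biweekly and two monthly visits, that is 5 + 2 + 2 = 9 in 17 weeks. The usual-care arm is contacted at least twice, by phone. Recurrences could therefore be detected and acted on unequally, although the rule itself is the same in both arms.

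**Step 4: illustration of size.** Let θ be the true effect in the absence of recurrence, p_I and p_C the shares withdrawn for recurrence before week 18 in the intervention and usual-care arms, and D the SRQ-DLV loss from an attack in SD units. Assume the treatment effect is otherwise the same in withdrawn patients.

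- Difference in all randomised patients: (θ − p_I·D) − (−p_C·D) = θ − (p_I − p_C)·D
- Difference in those observed, or imputed as if no attack occurred: θ
- Bias = (p_I − p_C)·D

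The arm size of 25 comes from the protocol (50 patients, 1:1). D from 0.5 to 1.5 and the withdrawal counts are assumptions, since the documents give neither.

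| Withdrawn, intervention v usual care | p_I − p_C | Bias at D = 0.5 | Bias at D = 1.0 | Bias at D = 1.5 |
|---|---|---|---|---|
| 1 v 1, 2 v 2 or 5 v 5 | 0 | 0 | 0 | 0 |
| 2 v 0 or 3 v 1 | 2/25 = 0.08 | 0.04 | 0.08 | 0.12 |
| 4 v 1 | 3/25 = 0.12 | 0.06 | 0.12 | 0.18 |
| 5 v 0 | 5/25 = 0.20 | 0.10 | 0.20 | 0.30 |

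Excess withdrawals in the intervention arm would inflate the apparent benefit. The same excess in usual care would shrink it by the same amount.

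**The case against.** **Nobody is removed from the analysis.** A reader might infer that recurrent patients are excluded and that the plan flatly contradicts intention to treat. The text does not say so. Data up to withdrawal are used, missingness is to be examined by arm, imputation is allowed for, and the sample size carries a 20% allowance for dropout or non-compliance. This stands: the defect is avoidable missing outcomes, not a declared exclusion. The allowance, however, protects precision and not against bias.

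**The sentence on no further assessments sits in the consent paragraph.** The paragraph on recurrence does not repeat it. This stands in part. The wording is general, and no outcome assessment is described for patients withdrawn by the team, so the natural reading is that there is none. At the least the text needs clarifying.

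**Patients on usual care may have a reason to leave.** The section says "Patients that want to withdraw from the study can continue with the rehabilitation programme outside the trial if they wish to do so", and a reader might infer that those doing badly while waiting would withdraw to get the programme sooner. The documents do not support this. No waiting time is given, staying in the trial leads to the programme straight after the week-18 assessment, and people who do not take part go on the ordinary waiting list. If poor outcomes were lost from usual care alone, that arm's mean would rise and the apparent benefit would shrink.

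**The bias could be set against the planning effect of 0.29.** The scale of that figure is unclear, so such a ratio means little. Read as a difference in SD units, it needs 2 × (1.960 + 1.282)² / 0.29² ≈ 250 patients per arm, whereas the protocol states 42 in total. Read as Cohen's f, it corresponds to a difference of about 0.58 SD.

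**The rule is the same in both arms.** Nothing in the documents suggests that the programme changes the risk of recurrence, and a recurrence need not involve the study arm. This also stands. It limits how large a bias should be expected.

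**Conclusion.** The concern holds as a weakness in follow-up. The protocol requires withdrawal after a recurrent attack, allows medical withdrawal by the team, and describes no outcome assessment afterwards. Withdrawal before week 18 leaves the primary outcome missing for a reason plausibly related to it, and no analysis can supply the post-attack scores.

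Bias in the arm difference is possible, not demonstrated. It needs such withdrawals to differ between arms in number or in their effect on function. Balanced withdrawals would bias the difference little. The 0 to 0.30 SD range rests wholly on assumed counts and assumed losses; the documents give no rate, size or direction. The case for acting is that scores not collected at week 18 are lost for good, while collecting them costs little.

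**What to change.** In Withdrawal procedures, separate three things: stopping the programme, medical withdrawal by the investigator or team (including after a recurrence), and a participant's withdrawal of consent to data collection. Only the last should end outcome collection. How a recurrence is handled clinically stays with the investigators and is not affected.

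With consent, keep collecting at least the week-18 SRQ-DLV from patients with a recurrence or withdrawn by the team. E-mail would do, as already planned for the follow-up questionnaires. Analyse these scores in the arm to which the patient was randomised. Report recurrences and withdrawals by arm, with timing relative to week 18. Add a sensitivity analysis that censors data at recurrence.

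The cost is a small amendment to the withdrawal and consent text and one questionnaire for what may be a few patients. Scores after an attack will add a little variability to the primary outcome.
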